# Birth ball for pregnant women in labour research protocol: a multi-centre randomised controlled trial

**DOI:** 10.1186/s12884-019-2305-8

**Published:** 2019-05-06

**Keywords:** Birth ball, Non-pharmacological, Pain relief, Pregnant women, RCT

## Abstract

**Background:**

Birth ball is one of the non-pharmacologic pain relief methods to help mothers cope with the labouring process. A randomised controlled trial (RCT) is conducted to evaluate the effectiveness, safety and harm of birth ball use by pregnant women in labour compared to treatment as usual group.

**Methods:**

A prospective multi-centre randomised controlled trial (RCT) will be conducted in Obstetrics and Gynaecological units of five public hospitals in Hong Kong, China. Data will be collected from March 2016 onward for 2 years. The target population is Chinese women with an uncomplicated singleton pregnancy at gestational age of 37 to 42 weeks. Participants are randomised based on parity (nulliparous and multiparous) and type of labour onset (spontaneous and induced). Women in the intervention group are actively offered and taught how to use a birth ball; those in the control group receive the usual midwifery care. The target sample size is 512. The primary outcome measures are maternal pain intensity, satisfaction with pain relief, sense of control in labour, assisted delivery and satisfaction with childbirth experience. Labour pain relief is measured by visual analogue scale (VAS). Other outcomes will be measured through four different validated questionnaires. To control for potential cluster effects, a linear mixed model will be used. An intention-to-treat analysis is adopted and performed by researchers unknown to subjects’ group allocation.

**Discussion:**

Results will provide rigorous scientific evidence for policy development and practice. We are using stratified randomisation according to potential confounders of parity and type of labour onset to give four possible combinations. If the results are favourable, it will facilitate systematic implementation to promote birth ball use for women in labour.

**Trial registration:**

Chinese Clinical Trial Register (ChiCTR), Registration number: ChiCTR-IIC-16008275, Date of registration 12 April 2016 (retrospectively registered), Date of enrolment of the first participant to the trial 1 March 2016.

## Background

Pain relief in labour was identified by an overwhelming majority (78%) of consumer groups and researchers to be one of the most important topics related to pregnancy and childbirth [1]. Given the frequent adverse effects of pharmacological analgesia and the healthcare cost associated with their complications, there is an incentive to use non-pharmacologic pain relief methods for pregnant women [2, 3]. Non-pharmacological methods can ease sensations of pain in a number of ways, by promoting women’s wellbeing, comfort, and sense of control in labour [4]; and the birth ball is one of the methods to help mothers cope with the labouring process and childbirth.

The birth ball, also called fitball or swiss ball, is a large ball commonly with a diameter of 55 cm or 65 cm. It provides a soft surface for women to sit on or lean against while carrying out simple exercises. Birth ball exercises can directly relieve women’s physical pain by improving pelvic dimensions, mobility and foetal positioning [5–7]. Concurrently, women’s psychosocial wellbeing can be enhanced when they take an active role in their own care, thereby promoting a sense of control over their care and body postures, balance and coordination.

Three local observational studies [8–10] reported strong acceptability and high satisfaction (over 90%) among Chinese women in Hong Kong public hospitals, who used birth balls during labour. Evidence for the use of a birth ball by pregnant mothers and related childbirth outcomes is insufficient. Thus far, there has been one systematic review with meta-analysis and four randomised controlled trials (RCTs) conducted in four countries: Spain, Taiwan, Iran, and Brazil [11–15]. These RCTs have been small, totalling 220 subjects, and thus the true effect size of a birth ball on pain control would be difficult to calculate due to chance and bias.

According to the result of the systematic review, more rigorous RCTs are necessary to evaluate the effect of birth balls on pain relief [11]. Searches in the World Health Organisation International Clinical Trials Registry Platform using keyword ‘birth ball’, returned six RCTs with subjects ranges from 32 to 128 [16]. Large scale clinical trials with adequate statistical power are needed to examine the effects of birth ball use by women in labour on various maternal, neonatal and infant outcomes, and system outcomes such as healthcare cost.

## Methods

A randomised controlled trial (RCT) is designed and the objective is to evaluate the effectiveness, safety and harm of birth ball use by pregnant women in labour compared to treatment as usual group. The research hypothesis is that participants randomised to the birth ball intervention group have better pain relief, higher satisfaction with pain control, higher sense of control in labour and higher satisfaction with childbirth experience, when compared to subjects in control group. This study protocol follows the SPIRIT checklist.

### Study setting

Recruitment for the study is conducted in all three regions of Hong Kong to enhance the generalizability of the results: Hong Kong Island (Pamela Youde Nethersole Eastern Hospital); Kowloon (Princess Margaret Hospital, Kwong Wah Hospital and Queen Elizabeth Hospital); and the New Territories (Prince of Wales Hospital). The study was initiated in March 2016 and continues until the end of 2017. Figure 1 is a Consort flow diagram of the progress through the phases of a parallel randomised trial of the intervention and control group.

**Fig. 1 Fig1:**
[figure not shown]
Consort flow diagram of the trial

### Randomisation and strata

This study adopts a two-arm (birth ball and control) randomised intervention-control trial design with block randomisation, as this is the most robust method of minimising selection bias and strengthening statistical power. We further enhance statistical power by using stratified randomisation according to potential confounders of parity (nulliparous or non-nulliparous) and type of labour onset (spontaneous or induced) – two strata give four possible combinations. Allocation is concealed by using sequentially numbered opaque sealed envelopes (in four separate sets) that contain group assignments determined by computer-generated random sequences. A research officer gives the sealed envelope to the health care worker who is intended to carry out the intervention. No intervention if subject is assigned to control.

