### Inclusion & exclusion criteria

For safety reason, pregnant women who are admitted to the hospital for labour and vaginal birth will not be considered unless they meet all the inclusion criteria. 1) Chinese women able to provide informed consent; 2) singleton pregnancy in cephalic presentation planned for vaginal birth; 3) gestational age of 37 to 42 weeks admitted into a single room in labour unit, either in spontaneous active labour and the second stage not imminent, or for induction of labour; 4) uncomplicated past obstetrical and antenatal history enabling them to be under independent midwifery care.

The exclusion criteria are 1) Multiple pregnancy; 2) foetal mal-presentation contraindicating vaginal delivery; 3) complicated pregnancy requiring close monitoring and restricted mobilization; 4) Caesarean delivery planned for this pregnancy; 5) any of the contraindication to use birth ball listed for each hospital (slightly varies due to different setting).

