## Discussion

This study draws data from five different sites across Hong Kong, which will increase the generalizability of results and enable easier systematic adoption of the intervention in other non-trial units. With the large sample size, single-blinded and stratified randomisation design, the results we have will provide reliable data. We are using stratified randomisation according to potential confounders of parity (nulliparous or non-nulliparous) and type of labour onset (spontaneous or induced) – two strata give four possible combinations.

Taking ethical concerns into consideration, we are not forbidding women in the control group to use the birth ball if they request them, and vice-versa; we will not forcefully limit their other pain relief options. All the subjects from control group will remain in the control arm in the intention-to-treat analysis. This is regarded as a major limitation of the study that is not likely to be solved. Furthermore, since we aim to examine the effectiveness of the birth ball intervention as a whole in real clinical settings, these possible confounders are not intentionally separated out, as they are integral parts of birth ball application and implementation. Different hospitals have different cultures and settings, and hence this can lead to deviation in practice and therefore bias. To standardise the research protocol and administering of the intervention, meetings and training are given to the midwives at all study sites before and periodically during recruitment. There will be subgroup analysis in each hospital.

Other limitations of this study include the concomitant use of other non-pharmacological pain relief methods during labour. It is common for pregnant women to use several analgesic methods at the same time. Although the time and method of all the analgesic methods are noted, the outcome effects of using a birth ball would become difficult to measure. Besides, in a busy antenatal and labour ward, the completion of research data by midwives and staff would be less than expected. Our researchers follow-up each participant and ensure all the relevant information from the medical record is reviewed. Although it would be impossible to blind the midwives or physiotherapists who teach birth ball, all the researchers will not be disclosed the case or control status of participants in the ward and during data analysis.

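### Hospital is neither a stratification factor nor a named model term, although the protocol calls hospital differences a source of bias and plans an analysis in each of the five hospitals

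*Protocol article*

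**What the plan says.** Randomisation and strata describes a "two-arm (birth ball and control) randomised intervention-control trial design with block randomisation". The factors are parity and type of labour onset, and "two strata give four possible combinations". On concealment: "Allocation is concealed by using sequentially numbered opaque sealed envelopes (in four separate sets"). On handover: "A research officer gives the sealed envelope to the health care worker who is intended to carry out the intervention". The abstract and the Discussion name the same two factors and no third.

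The trial runs in "Obstetrics and Gynaecological units of five public hospitals in Hong Kong, China". Study setting gives the reason for using several sites: "Recruitment for the study is conducted in all three regions of Hong Kong to enhance the generalizability of the results".

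Three statements bear on whether hospital matters:

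- Discussion: "Different hospitals have different cultures and settings, and hence this can lead to deviation in practice and therefore bias". The same paragraph offers meetings and training of midwives as the remedy, and announces a subgroup analysis in each hospital.
- Inclusion & exclusion criteria, last exclusion: "any of the contraindication to use birth ball listed for each hospital (slightly varies due to different setting").
- Statistical methods: the linear mixed model has midwife as a random effect. Hospital is not named as a term.

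**The concern.** The protocol singles out hospital as a source of practice differences and bias, lets eligibility vary by hospital, and intends to report by hospital. Yet hospital is missing from the stratification and from the terms named for the model. Training standardises how the intervention is delivered. It does not balance the arms within a hospital.

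At stake is balance and precision. Without a hospital stratum, chance can give one hospital noticeably more women in one arm. Differences between hospitals in usual care or case-mix then add noise to the arm comparison, and the by-hospital results rest on uneven arms. How much this matters depends on how the four sets serve five sites, which the article does not say.

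**Working it through.** **Step 1. The plan's own figure.** Inputs from Sample size and Statistical methods: Cohen's d = 0.25, alpha 0.05 two-sided, power 0.80, equal arms.

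- The normal approximation gives 252 per arm (504 in total). The noncentral t, as G*Power uses, gives 253 per arm (506 in total).
- Four strata × two arms = 8 cells; 506 / 8 = 63.25, rounded up to 64; 64 × 4 × 2 = 512, with power 0.806.

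So 512 reproduces. It is built from four cells of 64 + 64 = 128 women, with no hospital level. The point raised here does not change the required number.

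**Step 2. Set-up for within-hospital balance.** Taken from the document: 512 women, four strata of 128, five hospitals, permuted blocks, 1:1. Assumed, because the article gives neither: block size (4, with 8 as a check) and hospital shares (equal, or 35/25/20/12/8%). Equal shares give 512 / 5 = 102.4 women per hospital. Hospital-specific sets mean 5 × 4 = 20 lists, or 512 / 20 = 25.6 women per list on average. For each hospital the measure is |women in birth ball arm − women in control arm|; the worst of the five is taken in each run.

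**Step 3. Results (3,000 runs per scenario for the shared and hospital-specific lists; 5,000 for the batches).**

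| How the lists are used | Worst hospital, median difference | Worst hospital, 95th percentile | Chance that some hospital is 60:40 or worse | Overall arm difference, 95th percentile |
|---|---|---|---|---|
| One list per stratum shared across sites, equal shares | 13 | 23 | about 12% | 0 |
| Same, unequal shares | 13 | 23–24 | about 31% | 0 |
| Own four lists per hospital (20), either set of shares | 3–4 | 5–6 | at most 0.3% | 8–10 |
| Consecutive batch of a blocked list per hospital, equal shares, blocks of 4 | 4 | 7 | 0% | not computed |

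Block sizes 4 and 8 give nearly the same result for the shared list. Separate runs of the shared list with equal shares put the 60:40 chance at 10–11% and the chance of 55:45 or worse in some hospital at 73–74%. For consecutive batches the 55:45 chance is about 0.1% or less.

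**Step 4. What the imbalance means.** With 102.4 women in a hospital, a difference of 13 is (102.4 + 13) / 2 = 57.7 against 44.7, roughly 56:44. The efficiency of a split p : (1 − p) relative to 50:50 is 4p(1 − p). At 55:45 this is 4 × 0.55 × 0.45 = 0.99; at 60:40 it is 4 × 0.60 × 0.40 = 0.96. The by-hospital comparisons therefore lose at most a few per cent of efficiency from such imbalance. Their main limit is about 102 women each.

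**The case against.** The strongest reply is that the article does not say there are only four sets for the whole trial. Four sets match the four parity-by-onset cells and are compatible with four at each hospital or with batches sent to each site. Envelope logistics are commonly left to a full protocol. This stands as far as logistics go. A reader might infer that numbered envelopes cannot be opened in order across five sites, or that the audit check on concealment is lost. No passage describes opening out of sequence or one physical set being shared, so neither inference is supported.

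A reader might also suppose that splitting a blocked list between sites amounts to tossing a coin within each hospital. It does not: in a consecutive run, only the cut blocks at its two ends can be unbalanced, and the batch row in the table shows how little that is.

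Finally, the midwife random effect absorbs part of any hospital difference if midwives work at one hospital, and training is planned at all sites. Both are fair and limit the consequence.

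What the reply does not remove is that the choice of factors is not left open. The article names parity and onset repeatedly and never hospital, and the sample size has no hospital level. Exactly 64 per arm in each stratum is what one complete trial-wide list of 128 guarantees; hospital lists averaging 25.6 would not. That makes the trial-wide reading the more natural one, without proving it.

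**Conclusion.** The point holds as a modest design weakness that should be corrected. The protocol names hospital as a source of bias and plans results by hospital, but neither stratifies by it nor names it in the model.

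Its size depends on an unstated detail. With lists shared across sites, the worst hospital is typically about 13 women out of balance (95th percentile 23–24), and the chance of 60:40 or worse somewhere is about 10–12% with equal shares and about 30% with the unequal shares assumed. With hospital-specific lists the median is about 3–4. With consecutive batches per hospital it is already about 4, and little would be gained. These figures rest on assumed block sizes and hospital shares.

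A reader might conclude that leaving hospital out biases the trial's result. The documents do not support that. Randomisation without a hospital stratum still gives an unbiased overall comparison, and any site imbalance is due to chance. The gain is in balance and precision.

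**What to change.** **If allocation can still be changed:** add hospital as a stratification factor. Hold four parity-by-onset sets at each hospital (5 × 4 = 20), each with its own computer-generated blocked sequence and opened in number order, and amend Randomisation and strata to say so. In Statistical methods, add hospital, parity and labour onset as model terms alongside the midwife random effect.

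**If allocation is complete**, as is likely given that Study setting has the study ending at the close of 2017: add the hospital term to the model, report arm counts by hospital, and state how the four sets served the five hospitals.

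**Cost:** 20 sets to prepare instead of four, and incomplete final blocks that leave an overall arm difference of up to about 8–10 women out of 512 (95th percentile), against 0 when each trial-wide list is filled exactly. The hospital term uses 5 − 1 = 4 degrees of freedom, which is negligible at this size. The sample size does not change.

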### Sample size

Data to estimate sample size is only available from two randomised trials [13, 14]. Both trials have high risks of bias that likely lead to an overestimated effect size (Cohen’s d 0.90–1.34) in labour pain relief by birth ball, measured by visual analogue scale (VAS).

Without existing rigorous research enabling more accurate estimation of effect size, we re-calculated sample size with a conservative Cohen’s d of 0.25 in pain relief measured by VAS, alpha 0.05 and a power of 0.8. This was calculated using software G*Power (version 3.1.9.2). In order to have an equal number of participants in intervention and control groups, participants of each stratified block are further amended as 64 in each stratum. This gives a sample size of 512.

### Inclusion & exclusion criteria

For safety reason, pregnant women who are admitted to the hospital for labour and vaginal birth will not be considered unless they meet all the inclusion criteria. 1) Chinese women able to provide informed consent; 2) singleton pregnancy in cephalic presentation planned for vaginal birth; 3) gestational age of 37 to 42 weeks admitted into a single room in labour unit, either in spontaneous active labour and the second stage not imminent, or for induction of labour; 4) uncomplicated past obstetrical and antenatal history enabling them to be under independent midwifery care.

The exclusion criteria are 1) Multiple pregnancy; 2) foetal mal-presentation contraindicating vaginal delivery; 3) complicated pregnancy requiring close monitoring and restricted mobilization; 4) Caesarean delivery planned for this pregnancy; 5) any of the contraindication to use birth ball listed for each hospital (slightly varies due to different setting).

### Intervention and control

We recognise that the use of a birth ball is a complex intervention that changes the women’s usual care in several ways that some may consider confounding factors. Research suggests that splitting complex non-pharmacological pain relief methods into specific and placebo components may not be meaningful and may even produce false negative results [17]. Other non-pharmacological methods may include warm compresses, massage and transcutaneous electrical nerve stimulation.

Women in the intervention group are first offered and taught how to use the birth ball, followed by other non-pharmacological and pharmacological options, upon the women’s requests and advice from midwives. The existence and nature of placebo and the specific purpose of the trial is not disclosed at enrolment similar to other trials [18, 19].

Midwives or physiotherapists with certified birth ball training (42–76 in trial hospitals) or who attended birth ball teaching classes, provide instructions on birth ball exercises and supervise the participants (and her labour support person if present) using a birth ball. Instructions on four groups of exercises adapted from the Taiwan trial [13] and local study with high satisfaction [9] are given: 1) sit on birth ball; 2) kneel and lean forwards to hug the birth ball with both arms; 3) squat down; 4) variations of the above exercises together with a labour support person. Due to time constraints, group 1 and 2 are taught first and, if there is limited time, group 3 and 4 are left out. Women are suggested to use the birth ball for a minimum of 15 min in the beginning, then subsequently according to their own preferences of posture, type of exercise and pattern.

Women in the control group receive the usual midwifery care, without the midwives actively teaching and proactively suggesting women the use of the birth ball. Other non-pharmacological pain relief methods may include warm compresses, massage and transcutaneous electrical nerve stimulation. For ethical reasons, women in the control group can use the birth ball if they specifically request it. Their data remains in the control arm in intention-to-treat analysis.

### Outcome measurements

A Cochrane systematic review reported a list of core outcomes for labour pain control, agreed through a wide consultation with researchers and consumer groups [1]. These outcomes include many important clinical and patient-relevant measures relating to the mother and baby. The data is collected from participants’ medical record and questionnaire. A summary of the primary outcomes and corresponding measurements is listed in Table 1.

**Table 1 Tab1:** Summary of primary outcomes and measurements

Primary outcomes	Measurements
1. Pain intensity	Visual analogue scale (VAS)
2. Satisfaction with pain relief	American Pain Society – Patient Outcome Questionnaire–Modified (APS-POQ Modified)
3. Sense of control in labour	29-item Chinese validated Labour Agentry Scale (c-LAS)
4. Satisfaction with childbirth experience	Six Simple Questions (SSQ)

#### Primary outcomes

A simple and rapid visual analogue scale (VAS) of a 10-cm horizontal line, subdivided evenly with marks. Scores range from 0 (no pain) to 10 (extreme pain) are rounded to the nearest 0.1 cm, based on the women’s perceptions of pain at the time of assessment and during the peak of the last contraction at various time points: 1) on admission; 2) pre- and post-analgesia; 3) during labour, minimally every 2–4 h according to the phase of labour; 4) within 2 h of childbirth. This scale is the most widely used pain assessment scale in other birth ball studies [8–10, 13, 14]. Other primary outcomes are:

Satisfaction with pain relief
Modified satisfaction subscale from the American Pain Society – Patient Outcome Questionnaire (APS-POQ Modified) [20] is a 6-point scale (from ‘very dissatisfied’ to ‘very satisfied’) assesses women’s overall satisfaction of labour. The items regarding physicians are excluded.Additional questions on the willingness to use different analgesic methods in their next pregnancy and the most satisfied non-pharmacological method.
Sense of control in labour

A 29-item Chinese validated Labour Agentry Scale (c-LAS) [21, 22] is used. It has subjective statements such as ‘I felt confident’ and ‘I felt defeated’. Scores are given on a 7-point Likert scale (from ‘all the time’ to ‘almost never or never’).Satisfaction with childbirth experience

Six Simple Questions (SSQ) [23, 24] assesses women’s satisfaction with care during childbirth. Items are scored on a 6-point scale (from ‘strongly disagree’ to ‘strongly agree’), giving an overall score.

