### Statistical methods

Baseline characteristics of the two groups are compared by an ANOVA test for continuous variables and χ [2]-test for categorical variables. The primary outcomes are differences in the mean change of VAS pre- and post-intervention between birth ball and other control methods first on the list, and differences in total scores of APS-POQ modified, c-LAS and SSQ between groups. Secondary measures are differences in c-PBQ score and mode of delivery (assisted vaginal and caesarean); differences in proportions of breastfeeding, adverse effects, admission to special care baby unit or neonatal intensive care unit, five-minute Apgar score less than seven; and differences in cost.

To control for potential cluster effect, (e.g., participants by certain midwives) we will use a linear mixed model where the midwife is treated as a random effect. The basic model is a random intercept model with compound symmetry as the covariance structure. The data fitness is explored using alternative models, e.g., using different covariance structures, will be compared by the restricted maximum likelihood.

Intention-to-treat analysis is adopted and performed by researchers masked to subjects’ group allocation. A two-sided *P* value of 0.05 or less is considered statistically significant. Objective measures and clinical outcomes are validated independently by two researchers. To minimise missing data, research officers ensure complete data collection prior to subjects’ hospital discharge and remind subjects that a follow-up assessment takes place at 6 to 8 weeks post-partum.

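### The primary VAS change is not measured on a common clock in the two arms, and a control woman who uses no method has no defined pre/post pair

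*Protocol article*

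**What the plan says.** All references are to the Protocol article.

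- **Reading schedule (Primary outcomes).** VAS is taken "at various time points: 1) on admission; 2) pre- and post-analgesia", and then "3) during labour, minimally every 2–4 h according to the phase of labour; 4) within 2 h of childbirth". No time point is counted from randomisation.
- **Endpoint (Statistical methods).** The first primary outcome is "differences in the mean change of VAS pre- and post-intervention between birth ball and other control methods first on the list". The list is not shown. I read it as the first method recorded for each woman.
- **Control arm.** Randomisation and strata states "No intervention if subject is assigned to control". Intervention and control adds "Women in the control group receive the usual midwifery care, without the midwives actively teaching and proactively suggesting women the use of the birth ball". Alternatives are optional: "Other non-pharmacological pain relief methods may include warm compresses, massage and transcutaneous electrical nerve stimulation".
- **Ball arm (Intervention and control).** "Women are suggested to use the birth ball for a minimum of 15 min in the beginning"; after that, use follows the woman's preference.
- **Analysis (Statistical methods).** The analysis is by intention to treat. The model named is a linear mixed model with midwife as a random effect. No term for time or labour progress is named.
- **Sample size.** The trial is sized on VAS pain relief at Cohen's d = 0.25, alpha 0.05 and power 0.8, giving 512 women.

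**The concern.** A pre/post-intervention change needs an intervention time in both arms. In the ball arm there is one, the start of ball use. In the control arm there is one only if the woman takes up some other method, and she does so at a time and stage of labour of her own choosing. If she takes up none, the endpoint as worded is undefined for her.

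This has two consequences. First, dropping women without a pair makes the primary comparison one of method users, which conflicts with the stated intention-to-treat analysis. Second, among women who have a pair, nothing makes the interval or the stage of labour alike in the two arms. If pain changes as labour advances, the difference in mean change contains a timing component as well as any effect of the ball. Stratifying by parity and type of onset balances the women but not the reading times, which arise after randomisation. With a planning effect as small as d = 0.25, a modest timing component would matter.

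**Working it through.** **1. The plan's own figure.** Inputs from Sample size and Statistical methods: d = 0.25, two-sided alpha 0.05, power 0.80, equal arms.

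- Normal approximation: n per arm = 2 × (1.960 + 0.842)² / 0.25² ≈ 251.2, so 252 per arm, 504 in all.
- Two-sample t-test: 253 per arm, 506 in all.
- Spread over 8 cells (4 strata × 2 arms): 506 / 8 = 63.25, rounded up to 64, and 8 × 64 = 512.

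The stated 512 is reproduced and is not in question. It serves here only to show how small the planning effect is.

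**2. Is there a pair for each kind of woman?** The rules are set side by side.

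| Woman | Event that anchors the pair | Set by randomisation? |
|---|---|---|
| Ball arm, uses ball | Ball use; timing of the post reading not stated | Offer yes, timing no |
| Control, uses another method | First-listed method, with readings before and after it | No, self-selected |
| Control, uses no method | None | No pair defined |

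**3. How large a gap would matter?** The document gives no pain slope, no SD of change and no actual intervals, so all three are assumptions. With s the slope (cm/h), g the between-arm difference in mean interval (h) and SD the SD of change (cm):

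spurious d = s × g / SD, so the gap that equals the target is g = 0.25 × SD / s.

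At SD 2.5 cm, d = 0.25 is 0.625 cm:

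- s = 0.25 cm/h: g = 0.625 / 0.25 = 2.5 h
- s = 0.5 cm/h: g = 0.625 / 0.5 = 1.25 h
- s = 1.0 cm/h: g = 0.625 / 1.0 ≈ 0.6 h

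**4. Chance of a significant result with no true effect.** With 256 per arm, SE of d = √(2/256) = 0.0884.

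| s (cm/h) | g (h) | SD (cm) | Spurious d | P(reject) |
|---|---|---|---|---|
| 0.25 | 0.5 | 3.0 | 0.04 | 0.08 |
| 0.5 | 1.0 | 2.5 | 0.20 | 0.62 |
| 1.0 | 2.0 | 2.0 | 1.0 | about 1.0 |

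**5. Dilution.** Here g is a mean over the whole arm. If only a share p of controls had an interval longer by h hours, then g = p × h. With p = 20% and h = 2 h, both assumed, g = 0.4 h. At 0.25 cm/h that is 0.1 cm, or d = 0.04 at SD 2.5 and 0.05 at SD 2. The low end of the range is therefore a real possibility. If the mean intervals and the stages of labour were alike in the two arms, this component would be zero.

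**The case against.** **Controls do have an anchor.** The endpoint sentence names the first-listed other method, readings are required around analgesia, and the Discussion says the time and method of all analgesic methods are noted. This stands for controls who use a method: their pair may be quite like a ball user's. It does not make the comparison a randomised one, because uptake and timing are self-selected, and it gives nothing to a woman who uses no method.

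**The interval gap is not documented.** A reader might infer that ball women are read about 15 min apart and controls 2–4 h apart or after birth, so that the bias is known to favour the ball. The document does not support that. The 15 min is a suggested minimum for first use, not a reading time. The 2–4 h is a minimum reading frequency with no stated difference by arm. Nowhere is a no-method control's next routine reading said to serve as her post value. That pain rises over the interval is also an assumption, and a reading taken after birth could push the other way.

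**Exact windows belong in a full protocol or SAP.** This is true of window lengths. But the article does more than leave a window open. It states an event-anchored endpoint that, followed as written, has no common time origin and no value for some randomised women.

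**The data to repair this are largely planned.** Serial VAS readings, admission dilation, prior labour duration and contraction frequency are all collected. This stands, and it is why the repair is mainly one of definition and analysis.

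**Conclusion.** The point holds at medium severity. As worded, the primary VAS endpoint lacks a common clock across arms and is undefined for controls who use no method. It therefore does not deliver the intention-to-treat contrast that the plan claims, and it can confound any ball effect with labour progress.

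What is established is that the interval and labour stage are uncontrolled and can differ by arm, not that they do differ. Size and direction cannot be derived from the document. The only quantitative statement available is conditional: at SD 2.5 cm and slopes of 0.25 to 1.0 cm/h, a mean gap of about 2.5 down to 0.6 h would match d = 0.25, and smaller or diluted gaps would matter little. It would go too far to say that the pain result cannot be attributed to the ball at all. The sample size and the other primary outcomes are not affected by this point.

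**What to change.** Define the primary VAS contrast by randomised arm on time since randomisation.

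- **Baseline:** the last VAS before the envelope is opened.
- **Follow-up:** all routine in-labour readings of pain at the peak of the last contraction, in both arms.
- **Model:** the planned linear mixed model, extended with a woman-level random effect, time since randomisation, arm, arm-by-time, baseline VAS and the stratification factors. Admission dilation may be added.
- **Exclusions:** leave readings taken after birth out of this endpoint. Keep the event-triggered pairs around analgesia as descriptive.
- **Reporting:** give by arm the number of women who deliver before any follow-up reading.

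A single reading at a fixed time such as 2 h is simpler but should not be the only option. It may precede established labour in induced women, who fill two of the four planned strata (4 × 64 = 256 of 512), and it loses those who deliver earlier.

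**Cost.** No new scale is needed, but the time of each reading must be on record. Study setting has the study running to the end of 2017 and the article appeared in May 2019, so the change may have to be made in the analysis, using readings already taken where their times were recorded. Women who deliver early contribute no follow-up reading. The estimate becomes the effect of offering the ball over the course of labour, not the immediate effect of a session, and the report should say so.
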